**Objective:**

In an exploratory study, examine the feasibility of _HDS_EMG for rapid, non-invasive screening of hypoglossal nerve (CN XII) function and estimate the prevalence of hypoglossal neuropathy before and after oropharyngeal radiotherapy, and associate with patient-reported and clinician-graded functional outcomes. Machine learning performance will be measured through sensitivity, specificity, and F1 score, with a target area under the curve > 0.7 based on literature-reported EMG sensitivity and specificity.

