### Objectives

#### Primary objective: Examine the feasibility of _HDS_EMG for rapid, non-invasive screening of XII nerve function.

We plan to show that a machine learning algorithm trained on features of _HDS_EMG waveforms collected during a brief series of tongue tasks will detect CN XII neuropathy and grade its severity on a continuous, more sensitive scale than existing EMG. Time-frequency features extracted from _HDS_EMG will be used to detect tongue neuropathy grade using linear discriminant analysis, ensemble machine learning classifiers, and a neural network with a multiclass activation function, providing insight into the relationship between _HDS_EMG and tongue function degradation. Tongue _HDS_EMG will also be decomposed into estimates of constituent MU spike trains for analysis with a convolutional neural network.

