### Needle electromyography and nerve conduction

Intramuscular EMG will assess insertional activity in the genioglossus muscle, innervated by CN XII, as a marker of denervation [23]. Needle EMG is reported to have an inter-operator reliability of 0.53 [24]. EMG recordings will be conducted by a cancer neurologist fellowship trained in clinical neurophysiology and denervation potentials graded per standard neurologist’s grading:

0 - None

1 - Persistent, single train of potentials in at least two areas

2 - Moderate number of potentials in three or more areas

3 - Many potentials in all areas

4 - Full interference patterns of potentials

EMG and NCS may also be performed in the trapezius muscle (innvervated by CN XI), as the region is easily accessible for non-invasive testing and represents a muscle within the irradiated field with lower cranial nerve innervation. Both quantitative and qualitative EMG may be assessed [25]. Needle EMG will not be conducted if platelets are < 50,000. The intramuscular EMG will require a clinical visit with the neurologist.

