### Outcomes definition

#### Primary objective.

For analysis of the primary objective, the primary endpoint will be _HDS_EMG classification of XII neuropathy (yes/no, then graded) in relation to the gold-standard needle EMG classification. We expect to show that features such as frequency of interference patterns and tongue fasciculations correlate between _HDS_EMG and needle EMG, demonstrating that _HDS_EMG is a feasible, rapid, non-invasive biomarker for tongue neuropathy. We will consider _HDS_EMG feasible for this exploratory analysis if more than 80% of the signal recordings meet the quality criteria. We also expect that a neural network with a multiclass activation function will grade tongue neuropathy progression on a continuous scale.

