### Evaluation criteria

The performance of machine learning classifiers will be divided into two classification settings: binary (CN XII neuropathy vs. no confirmed CN XII neuropathy) and multiclass (neuropathy grade). In binary classifiers, we aim for AUC ≥ 0.70 to support _HDS_EMG as an inexpensive, non-invasive quantitative metric for screening OPC survivors for CN XII neuropathy. Narayanaswami et al. report that electromyographers with 10–20 years of experience have a diagnostic sensitivity of 0.77 and a specificity of 0.71 for neuropathy. [24] This will serve as our benchmark for reliable performance for all binary model development. For the 10% validation set, we will measure model performance simply by the percentage of correctly diagnosed cases of neuropathy. As a secondary validation outcome, we will compare the _HDS_EMG neuropathy severity grade with the gold-standard needle EMG grades.

Multiclass classification will use micro- and macro-F1 scores to evaluate the validity of a refined CN XII neuropathy grade prediction. Saliency mapping for the CNN will reveal which signal regions contribute to each neuropathy grade prediction. Machine learning models will be evaluated using SHapley Additive exPlanations (SHAP) to investigate which features contribute to the model predictions [39].

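### The binary classifier has two performance bars that do not agree, and one of them (0.77/0.71) is electromyographers' own accuracy, which is no yardstick for agreement with needle EMG

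*Protocol article*

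**What the plan says.** The abstract's Objective sets a "target area under the curve > 0.7 based on literature-reported EMG sensitivity and specificity". The Evaluation criteria section repeats the threshold ("In binary classifiers, we aim for AUC ≥ 0.70 to support" the use of HDsEMG for screening). It then cites a study in which electromyographers with 10 to 20 years of experience "have a diagnostic sensitivity of 0.77 and a specificity of 0.71 for neuropathy", and continues: "This will serve as our benchmark for reliable performance for all binary model development". These are the only sensitivity and specificity figures in the document.

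Under Outcomes definition, the primary endpoint is the HDsEMG classification of neuropathy "in relation to the gold-standard needle EMG classification". The section on needle electromyography takes an inter-operator reliability of 0.53 for needle EMG from the same cited source. The primary objective says the algorithm will detect neuropathy and "grade its severity on a continuous, more sensitive scale than existing EMG".

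The article does not show how 0.70 was reached. It does not say what truth the 0.77 and 0.71 were measured against, or which bar decides if a model meets one and misses the other.

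**The concern.** There are two problems, and the second matters more.

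First, a model can reach the AUC target and fall well short of the sensitivity and specificity benchmark. Both are stated for the binary classifier, which carries the primary endpoint. Without a rule, the choice between them could be made after the results are seen.

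Second, the benchmark is the accuracy of people reading EMG, judged against some other truth. In this study the needle EMG reading is the truth, so what is measured is agreement with a reader. Reaching 0.77/0.71 on that scale could be read as matching an experienced electromyographer, which it would not show. The Discussion plans to use the resulting sensitivity and specificity to size future studies, so the misreading would carry forward.

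**Working it through.** **Inputs.** AUC target 0.70 (abstract, Evaluation criteria). Sensitivity Se = 0.77 and specificity Sp = 0.71 (Evaluation criteria). Expected post-treatment prevalence about 40%, and 5% pre-RT and 42% post-RT in groups of 12 and 24 (Data analysis and machine learning plan). The planned mix gives (12 × 0.05 + 24 × 0.42)/36 = 10.68/36 = 29.7%, or about 11 positives in 36.

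**Step 1. Which AUC corresponds to 0.77/0.71?**
- Single-point trapezoid: (0.77 + 0.71)/2 = 0.74. This is the minimum for a concave ROC curve.
- Equal-variance binormal: z(0.77) + z(0.71) = 0.739 + 0.553 = 1.292; AUC = Φ(1.292/√2) = 0.82.
- Constant odds ratio: OR = (0.77/0.23) × (0.71/0.29) = 8.20; AUC = OR/(OR − 1)² × (OR − 1 − ln OR) = 0.81.
- If the curve is only required to be monotone, the bounds are 0.77 × 0.71 = 0.547 and 1 − 0.23 × 0.29 = 0.933.

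The stated 0.70 is not reproduced by any of the three standard conversions.

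**Step 2. What does a model at AUC 0.70 deliver?** Under the binormal form, √2 × z(0.70) = 0.742.
- Specificity at sensitivity 0.77: Φ(0.742 − 0.739) = 0.50, against 0.71.
- Sensitivity at specificity 0.71: Φ(0.742 − 0.553) = 0.57, against 0.77.

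Such a model meets the first bar and misses the second.

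**Step 3. What would agreement with needle EMG look like if the reader's true accuracy were 0.77/0.71?** Applying these figures to this study's reader is an assumption. Let p be the true prevalence. A perfect HDsEMG scored against needle EMG shows:
- apparent sensitivity = p·Se / [p·Se + (1 − p)(1 − Sp)]
- apparent specificity = (1 − p)·Sp / [(1 − p)·Sp + p(1 − Se)]

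At p = 0.40 these are 0.308/0.482 = 0.64 and 0.426/0.518 = 0.82.

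| True prevalence | Apparent sensitivity, perfect test | Apparent specificity, perfect test |
|---|---|---|
| 30% | 0.53 | 0.88 |
| 40% | 0.64 | 0.82 |
| 50% | 0.73 | 0.76 |

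A perfect test misses the 0.77 sensitivity mark in every row. A test exactly as accurate as the reader, with conditionally independent errors, would show 0.60/0.62 at 40% prevalence. Parity with needle EMG therefore does not appear as 0.77/0.71.

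**Step 4. Would a target of 0.74 be better?** Under the Step 3 assumption, a perfect binary test has a single-point AUC against needle EMG of (0.639 + 0.822)/2 = 0.73 at 40% prevalence and 0.70 at 29.7%. A target of 0.74 would lie above both. Precision cannot separate the two targets either: with 11 positives and 25 negatives, the Hanley-McNeil standard error at AUC 0.70 is about 0.10, a 95% half-width of about 1.96 × 0.10 = 0.20.

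**The case against.** Several points on the other side are sound and limit what can be claimed.

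- *The 0.70 is not shown to be a miscalculation.* A reader might infer an arithmetic error. The abstract says the target is based on the literature figures, not calculated from them, and no formula is given. A round floor just below both figures fits that wording. What stands is that the bars differ, not that a sum is wrong.
- *The figures do not strictly imply an AUC of at least 0.74.* That holds only for a concave ROC curve; the monotone-only lower bound is 0.547.
- *The two bars might be a minimum and an aspiration.* Both could be met together, and the only explicit feasibility rule is that more than 80% of recordings pass quality criteria. This is fair, but the article does not describe the bars as tiers and gives no rule for a split result.
- *The claim of a more sensitive scale is not shown to be untestable.* A reader might take it as higher detection sensitivity, which a comparison with needle EMG alone could not show, because each extra case would count as a false positive. But the text speaks of a scale, and the Introduction contrasts coarse 0 to 4 grading with continuous grading. Finer grading is the natural reading, and correlations with L-ROM and tongue pressure are already planned.
- *The benchmark does not establish a clash with the power inputs.* A reader might infer that specificity 0.71 makes at least 29% of pre-RT patients needle-positive, against the 5% assumed. That transfers an outside figure to this muscle, population and reader, and the article does not support the transfer.
- *The study is exploratory.* The Discussion says so and acknowledges the single reader. That tempers the conclusions but does not make 0.77/0.71 a suitable yardstick for agreement with needle EMG.

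**Conclusion.** The concern holds as an inconsistency and a misapplied benchmark. The AUC target and the 0.77/0.71 benchmark are different bars: the latter corresponds to an AUC of 0.74 to 0.82, given a concave ROC curve and depending on its form. A binormal model at 0.70 falls 0.21 short on specificity at the benchmark sensitivity.

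The main conclusion needs no numerical assumption: accuracy of needle EMG readers cannot serve as the standard for agreement with needle EMG, so meeting it would not show equality with needle EMG. The size of the distortion does rest on assumptions. The figures 0.64/0.82 at 40% prevalence (0.53/0.88 at 30%, 0.73/0.76 at 50%) require that 0.77/0.71 apply to this study's reader and that the stated prevalence is the true one. For an imperfect HDsEMG the size also depends on how far its errors follow the reader's; positively correlated errors would raise the apparent agreement.

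This should be changed, because it alters what the study can conclude, but it does not threaten the conduct of an exploratory study.

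**What to change.** 1. Keep AUC of at least 0.70 as the single exploratory target for the binary classifier, written the same way in the abstract and the Evaluation criteria, and report it with a 95% CI computed at patient level. Delete the phrase "based on literature-reported EMG sensitivity and specificity". Do not raise the target to 0.74: that number comes only from the figures being set aside.
2. Remove 0.77/0.71 as the benchmark for binary models. The cited study can stay as background on the imperfection of needle EMG.
3. Report results as positive and negative agreement with needle EMG, not as diagnostic sensitivity and specificity.
4. State that the more sensitive scale means finer grading, supported by the planned correlations with L-ROM and tongue pressure, and not higher detection sensitivity than needle EMG.

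The cost is protocol wording and one confidence interval; no new data are needed. The downside is that the study loses its literature comparator, and 0.70 then stands as a chosen exploratory threshold.

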All accepted signals are divided into 2-second segments for feature extraction. The Discrete Wavelet Transform (DWT) will be used to extract time series features (waveform length, zero crossings, slope signal changes, root mean square, autoregressive coefficient, mean absolute value, and integrated mean absolute value) and time-frequency features (mean instantaneous frequency, mean first derivative, amplitude-modulated bandwidth, frequency-modulated bandwidth, and spectral moment of power spectral density) [32]. We will perform Mann—Whitney U-tests with α = 0.05 to determine whether these features are relevant to neuropathy through the following comparisons: reduced recruitment vs. no reduced recruitment; polyphasia vs. no polyphasia; increased amplitude vs. no increased amplitude; and increased duration vs. no increased duration. To further demonstrate the clinical relevance of _HDS_EMG features, we will use Pearson’s Correlation Coefficients and multiple regression analysis to express correlations between _HDS_EMG features and tongue functional outcomes (L-ROM and IPOI pressure).

The full dataset will be partitioned patient-wise into 70% for training, 20% for development, and 10% for validation. Features from the training set that discriminate neuropathy severity will be selected using linear discriminant analysis. Missing data may occur during time-frequency feature extraction, as some calculations can trigger divide-by-zero errors, especially for low-frequency components. If this occurs, such examples will be rejected as artifacts. If any class label is represented by less than 10% of the data, recording-wise mean imputation will be performed to augment the number of unique examples in the underrepresented classes.

We intend to train an initial decision tree and support vector machine (SVM), followed by ensemble methods using both trees and SVMs, where possible: Random Forest Classifier, Gradient Boost, and Bagging. We will also train a neural network classifier with a softmax activation function for multiclass classification. Hyperparameter optimization will be performed using 5-fold cross-validation and verified using the development set. To account for potential class imbalance, all ensembled learning methods will be trained using class-weighted sampling to ensure that individual classifiers within the ensemble see class-balanced subsets of the data. Machine learning will be performed using SciKit Learn [33].

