For the secondary objective, we will estimate the prevalence of neuropathy at three time points (pre-treatment, 3–6 months after treatment, and 18 months to 5 years after treatment), along with exact 95% binomial confidence intervals (CIs). Logistic regression models will be fit with XII neuropathy as a binary response variable adjusted for sampling weights and clinical covariates. For hypothesis 1.1, we will model time as a binary variable (0 = pre-RT and 1 = post-RT), pooling the two post-RT groups (n = 24) versus the pre-RT group (n = 12). Time will be included as a continuous variable (i.e., months pre- or post-RT). We expect an exploratory sample of 36 patients who consent to tongue testing, with equal allocation across 12 patients in one of three groups based on the timing of EMG collection relative to their cancer treatment: pre-treatment, early post-treatment, and late post-treatment. Twelve patients per group ensure a maximum half-width of the 95% CI of 0.29. After treatment, we expect the prevalence of neuropathy to be approximately 40%, based on our published data that 10% of survivors develop clinically detectable neuropathy [9,37]. Unpublished data from the NIH intramural laryngeal study section found that 90% of chronic radiation-associated dysphagia cases have EMG-detectable denervation [38]. The investigators’ data show that 100% of patients with DIGEST grade ≥2 dysphagia who are ≥ 2 years disease-free HNC survivors have EMG detectable neuropathy as early as 2 years post-RT (38% of whom have subclinical neuropathy). Logistic regression on a binary independent variable (pre- vs. post-RT) with a sample size of 36 (n = 12 pre- and n = 24 post-RT) achieves 80% power (α = 0.10) to detect a difference in the probability of neuropathy from 5% pre-RT to 42% post-RT.

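### The 10% validation set is 3 or 4 patients with about one expected neuropathy case, so it cannot assess the AUC target or the sensitivity and specificity benchmark

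*Protocol article*

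**What the plan says.** Under Outcomes definition, the primary endpoint is the classification of CN XII neuropathy by surface EMG (yes/no, then graded) against needle EMG.

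The Data analysis and machine learning plan gives the sample and the split:
- "We expect an exploratory sample of 36 patients who consent to tongue testing"
- "The full dataset will be partitioned patient-wise into 70% for training, 20% for development, and 10% for validation"
- "Hyperparameter optimization will be performed using 5-fold cross-validation and verified using the development set"

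Evaluation criteria sets an AUC target of at least 0.70 for the binary classifiers. It takes a published sensitivity of 0.77 and specificity of 0.71 as the benchmark for binary model development. For the 10% validation set it then says that "we will measure model performance simply by the percentage of correctly diagnosed cases of neuropathy". The next sentence adds a secondary validation outcome: predicted grade compared with needle EMG grade. The Discussion allows only exploratory interpretation, but also says the work will establish benchmark sensitivity and specificity values to inform future sample sizes.

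**The concern.** The validation set is the only part of the data not used to fit or tune a model, so it is the only place where the plan could obtain an independent estimate for the primary endpoint. Ten per cent of 36 patients is too few to estimate anything. The metric named for the set does not match the AUC target or the sensitivity and specificity benchmark. At stake is what the study can report: the performance figures left to quote would come from data that shaped the models, and the Discussion intends such figures to size later studies.

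**Working it through.** **Inputs (all from the Data analysis and machine learning plan unless noted).** 36 patients, 12 pre-RT and 24 post-RT. Neuropathy rates 5% pre-RT and 42% post-RT in the power statement ("to detect a difference in the probability of neuropathy from 5% pre-RT to 42% post-RT"), with about 40% post-RT given as the expected prevalence. Split 70/20/10 by patient. Needle EMG grades 0 to 4 (Needle electromyography and nerve conduction).

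**The protocol's own figure.** It states no precision for the validation set, but it does state 80% power at α = 0.10 from the same rates.
- Pooled rate = (12 × 0.05 + 24 × 0.42)/36 = 0.297.
- Null SE = √(0.297 × 0.703 × (1/12 + 1/24)) = 0.1615.
- Alternative SE = √(0.05 × 0.95/12 + 0.42 × 0.58/24) = 0.1188.
- Two-sided power = Φ((0.37 − 1.645 × 0.1615)/0.1188) = 81.0%.

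This agrees with the stated 80%, so the rates are used below as the protocol means them.

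**Size of each part.** 36 × 0.70 = 25.2; 36 × 0.20 = 7.2; 36 × 0.10 = 3.6. The validation set is 3 or 4 patients.

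**Expected cases.**
- Post-RT 40%: 12 × 0.05 + 24 × 0.40 = 10.2 cases in 36 (28.3%).
- Post-RT 42%: 12 × 0.05 + 24 × 0.42 = 10.7 cases in 36 (29.7%).
- Validation set: 3.6 × 0.283 to 3.6 × 0.297 = 1.02 to 1.07 cases.
- Development set: 7.2 × 0.283 to 7.2 × 0.297 = 2.0 to 2.1 cases.

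**Cases drawn into the validation set.** With K cases in 36 and m patients drawn without stratification, P(no case) = C(36−K, m)/C(36, m) and P(one case) = K × C(36−K, m−1)/C(36, m).

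| K | m | No case | Exactly one |
|---|---|---|---|
| 11 | 3 | 2300/7140 = 32% | 3300/7140 = 46% |
| 10 | 3 | 2600/7140 = 36% | 3250/7140 = 46% |
| 11 | 4 | 12650/58905 = 21% | 25300/58905 = 43% |
| 10 | 4 | 14950/58905 = 25% | 26000/58905 = 44% |

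**Metric read as sensitivity.** It is undefined in 21–36% of draws. One case is the most likely count. The result is then 0% or 100%, and the exact 95% CI for 1/1 is 2.5–100%. A rule that labels every patient neuropathic scores 100% whenever there is a case.

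**Metric read as accuracy.** When all n are correct, the exact lower limit is 0.025^(1/n): 29% for 3/3 and 40% for 4/4. For 3/4 correct the interval is 19–99%. A rule that labels every patient healthy is fully correct whenever no case is drawn, again 21–36% of the time.

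**Against the stated targets.** With one case and three non-cases, AUC can only be 0, 1/3, 2/3 or 1. With one case and two non-cases it can only be 0, 1/2 or 1. With no case it does not exist. The grade comparison uses the same 3 or 4 patients, who cannot span five grades.

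**What all 36 patients would give if each were scored out-of-fold (11 cases, 25 non-cases).**
- Sensitivity 8/11: exact 95% CI 39–94%.
- Specificity 18/25: 51–88%.
- AUC 0.70 (Hanley–McNeil): Q₁ = 0.70/1.30 = 0.538 and Q₂ = 2 × 0.49/1.70 = 0.576. SE = √[(0.21 + 10 × (0.538 − 0.49) + 24 × (0.576 − 0.49))/275] = 0.100. The 95% CI is 0.50–0.90, and with 10 cases it is about the same.

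**The case against.** The study calls itself exploratory. The Discussion names N = 36 as a limit on generalisability and leaves a blinded multi-site test set to future work. The feasibility criterion under Outcomes definition, more than 80% of recordings passing quality checks, does not depend on the validation set. All of that stands and limits the consequence. It does not rescue the hold-out: the size of that set is nowhere acknowledged, the primary endpoint is classification, and reaching the AUC target is meant to support screening use.

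The plan also counts hundreds of millions of sampled values and offers to analyse subsets to enlarge the data. Samples, channels, 2-second segments and repeat visits are clustered within patients, and the split is by patient, so none of these adds an independent validation unit.

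Several stronger readings are tempting, and the document does not support them:
- A reader might infer that validation rests on one metric alone. It does not, because the grade comparison is a second outcome, although on the same patients.
- A reader might infer that the metric is certainly sensitivity. The wording also permits accuracy, and the Objective in the Abstract names sensitivity, specificity and F1 as performance measures.
- A reader might infer that many models compete and the best will be chosen on the development set. No such rule is stated. The development set verifies hyperparameters, and the Fig 1 caption describes a final multitask network that makes the final prediction. What is missing is a statement that this network is the model judged against the AUC target, which is set for binary classifiers in general.
- A reader might infer that the result is always 0% or 100%. Under the sensitivity reading that applies to draws with exactly one case, 43–46% of the time. Two or more cases do occur.

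**Conclusion.** The concern holds. As written, the hold-out cannot confirm or refute AUC of at least 0.70 or the 0.77/0.71 benchmark, under either reading of its metric. The cross-validation and the development set of about 7 patients (about 2 cases) are used for tuning, so they give no independent estimate either. The primary classification endpoint therefore has no usable independent performance estimate.

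This rests on 36 patients being accrued, on the protocol's own prevalence rates, and on a random split not stratified by neuropathy status, since no stratification is stated. Stratifying would secure about one case but would not narrow the intervals. The exploratory label lowers the consequence without removing the defect, which is worth correcting before the analysis begins.

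**What to change.** Replace the fixed 70/20/10 split with nested cross-validation at patient level over all 36 patients. Use outer folds stratified by binary neuropathy status, or leave one patient out. Carry out feature selection, imputation for under-represented classes and hyperparameter tuning within the training folds only.

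Report out-of-fold AUC, sensitivity and specificity with patient-level 95% CIs, in place of the percentage of correctly diagnosed cases. State that the final network in Fig 1, or another single named model, is the one judged against the AUC target, and label the other models exploratory. Treat the five-grade results as descriptive.

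The cost is computing time and protocol wording, with no new data or visits. The loss is a single frozen hold-out set, which at 3 or 4 patients carries almost no information. The gain is limited: the estimates become comparable with the stated targets but stay imprecise, so they should be reported as exploratory.

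### With about 11 neuropathy cases expected among 36 patients, a five-grade classifier cannot be reliably trained, tuned by patient or tested on held-out patients; the graded result should be descriptive

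*Protocol article*

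**What the plan says.** The section Needle electromyography and nerve conduction grades denervation potentials on five levels, 0 to 4. Outcomes definition makes HDsEMG classification against needle EMG the primary endpoint, first as presence or absence and then by grade. It counts any grade above 0 as neuropathy.

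Data analysis and machine learning plan fixes the sample: "We expect an exploratory sample of 36 patients who consent to tongue testing, with equal allocation across 12 patients in one of three groups". It also fixes the split: "The full dataset will be partitioned patient-wise into 70% for training, 20% for development, and 10% for validation". Signals are cut into 2-second segments, and hyperparameters are tuned by 5-fold cross-validation and checked on the development set. For rare classes it says: "If any class label is represented by less than 10% of the data, recording-wise mean imputation will be performed". Ensemble models also use class-weighted sampling. The adequacy of 36 patients for the classifier is argued from the number of recorded signal values, not from patients or cases per grade.

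Evaluation criteria sets the graded metric: "Multiclass classification will use micro- and macro-F1 scores to evaluate the validity of a refined CN XII neuropathy grade prediction". For the 10% validation set it plans the percentage correctly diagnosed and, as a secondary outcome, a comparison of predicted grade with needle-EMG grade.

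**The concern.** Each patient brings a large volume of signal but only a few independent examples of a grade. What a classifier can learn about grade 3, and what a held-out test can say about it, depends on how many patients have grade 3. Millions of samples from one such patient cannot separate the grade from that patient's other characteristics.

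The grade scale, sample size, planning prevalence, patient-wise split and macro-averaged metric are each stated, but they do not fit together. If grades are nearly empty, a macro-F1 mostly reflects which patients fell into which part of the split. The severity-grading half of the primary endpoint could then be neither supported nor refuted. The protocol states no rule for a sparse or empty grade other than imputation and reweighting.

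**Working it through.** **Inputs from the protocol article (Data analysis and machine learning plan).** 12 pre-RT and 24 post-RT patients; neuropathy 5% and 42%; split 70/20/10, that is 25.2 / 7.2 / 3.6 patients, taken as 25 / 7 / 4.

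**The plan's own figure first.** The plan puts its power at 80% with α = 0.10 for this target: "detect a difference in the probability of neuropathy from 5% pre-RT to 42% post-RT". Two-sided test of two proportions with pooled null variance:
- pooled rate = (12×0.05 + 24×0.42)/36 = 10.68/36 = 0.297
- null SE = √(0.297×0.703×(1/12 + 1/24)) = 0.1615
- alternative SE = √(0.05×0.95/12 + 0.42×0.58/24) = 0.1188
- power = Φ((0.37 − 1.645×0.1615)/0.1188) = 0.81

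The sample-size formula for logistic regression on a binary covariate gives 35.2, so 36. The planning rates are therefore read correctly.

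**Expected cases.** 12×0.05 + 24×0.42 = 10.7 (10.2 if the post-RT rate is 40%).
- By part of the split: training 10.68×0.7 = 7.5; development 10.68×0.2 = 2.1; validation 10.68×0.1 = 1.1.
- Per neuropathic grade, if equal: 10.68/4 = 2.7 patients, or 2.7/36 = 7.4%. This is already below the plan's 10% trigger if the trigger is read by patient. About 2.7×0.7 = 1.9 of them are in training.

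**Assumption.** The protocol gives no spread over grades 1 to 4, so three were tried: equal (25% each), mild skew (40/30/20/10) and strong skew (60/25/10/5).

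**Simulation.** Cases binomial by group, grades multinomial among cases, random 25/7/4 patient split:

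| Share of cohorts with | Equal | Mild skew | Strong skew |
|---|---|---|---|
| all five grades among 36 patients | 77% | 56% | 26% |
| all five grades in training (25) | 52% | 35% | 13% |
| at least 2 training patients in every grade | 7% | 3% | 0.3% |
| at least 5 training patients in every grade | 0% | 0% | 0% |
| all five grades in development (7) | 1.4% | 1.0% | 0.3% |
| all five grades in validation (4) | 0% | 0% | 0% |

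Repeat runs agree to within about one percentage point. The last row needs no simulation, because four patients cannot hold five grades. About 24% of cohorts have no neuropathy case at all in validation.

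**Size needed, for scale.** One patient of each grade 1 to 4 in each of five patient-wise folds needs 4×5 = 20 training cases. That is 20/0.7 = 28.6 cases overall, or 28.6/0.297 = about 96 patients, even with equal grades.

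**Sensitivity to prevalence.** At 90% post-RT prevalence, expected cases are 0.6 + 21.6 = 22.2. With equal grades, all five appear in training in 94.5% of cohorts and in development in 15%. At least 5 training patients in every grade occurs in 0.01%. Higher prevalence eases training but not held-out evaluation.

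**The case against.** The strongest reply is that nothing here stops the analysis from running, and that reply is right as far as it goes. A reader might infer that five-grade training, tuning and macro-F1 cannot be carried out as written. The documents do not support that, for these reasons:
- Models train on 2-second segments, 140/2 = 70 per patient in one pass of the tasks. A grade can be trained on whenever one training patient has it.
- The article says patient-wise of the 70/20/10 partition only. It does not give the unit of the 5-fold tuning, and a fold may lack a class without the procedure failing. A requirement of five patients per grade is therefore a condition for sound patient-wise tuning, not something the protocol sets. Segment-level folds would run, but would put one patient in several folds.
- The data on which F1 is computed are not stated, so F1 is not bound to the development or validation set. Micro-F1 does not average over grades. An article may leave both details to a fuller plan.
- A reader might also infer that at most two neuropathic grades can ever reach the 10% floor. That holds only at the expected count: 12 or more cases, enough for three grades of four patients, occur in about 37% of cohorts. The floor is also set on the data, not on patients.

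The study calls itself exploratory, concedes that its sample size could not be optimised, and sets no F1 threshold. Its numeric targets concern binary AUC and signal quality. So no stated go/no-go decision rests on macro-F1.

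What these points leave untouched is the number of patients. Imputed examples, class weights, both tongue sides and data subsets add recordings, not independent cases, and none can fill an empty grade. The exploratory label does not say how an empty grade will be handled, while the grade remains part of the primary endpoint.

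**Conclusion.** The point holds in a limited form. With about 11 expected cases, five grades cannot be reliably trained, tuned by patient or evaluated on held-out patients under the 70/20/10 split. It is a matter of reliability, not impossibility of execution. The case count follows from the protocol's own rates. The presence figures also rest on the assumed grade spreads and a random split into 25, 7 and 4. The conclusion is the same for all three spreads. The grade comparison planned for the validation set cannot cover the scale under any spread. The binary classification is not affected by this argument about grades. This should be corrected, but it does not undermine the study as a whole.

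**What to change.** Change the wording of Outcomes definition, Data analysis and machine learning plan, and Evaluation criteria as follows:
- Keep the binary classification as the formal analysis and label the graded result descriptive.
- Report the 0-4 confusion table and the number of patients in each grade.
- Compute micro- and macro-F1 once, on out-of-fold predictions pooled over all 36 patients from patient-grouped cross-validation. Nest tuning inside, and keep all segments of a patient in one fold. If a grade has no patient among the 36, say so beside the score.
- Do not count imputed examples as added cases.
- If a collapsed-grade score is wanted, fix the cut before the data are seen. State how often it would be usable: with levels 0, 1 and 2-4 and a minimum of 5 patients per level, it would fall back to binary in about 68% to 89% of cohorts under the assumed spreads.

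No new data are needed. The cost is that there is no separate locked hold-out set and no formal claim about individual severity grades. The pooled F1 would still rest on very few patients per grade, which is why it should be read descriptively.
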